At the community level, the primary outcome includes net change in the proportion of RDW with any of the 3 HRP conditions (anemia, PIH, and APH) whose problem was resolved prior to delivery and who reported satisfaction with the management of the condition, from baseline to end line, in intervention versus control arm. Satisfaction level of RDW is measured using a 5-point Likert scale on the topics of “attitude and behavior of staff,” “cleanliness and hygiene,” “comfort and care,” and “overall satisfaction with management of HRP condition at the facility.”

The community-level secondary outcomes include net change in proportion of RDW who received the complete ANC package during their last pregnancy*,* from baseline to end line, in intervention versus control arm. Also includes the net change in proportion of RDW who were sensitized about HRPs by ANM or MO during their last pregnancy*,* during baseline and end line, in intervention versus control arm. Other secondary outcomes include net change in the mean gestational month of first diagnosis of 3 HRPs by an ANM*,* from baseline to end line, in intervention versus control arm, and net change in the proportion of RDW diagnosed with any of the 3 HRPs who received protocol-based management or referral from an ANM*,* from baseline to end line, in intervention versus control arm. We also measure the net change in proportion of RDW diagnosed with any of the 3 HRPs, received protocol-based management or referral from MO*,* from baseline to end line in intervention versus control arm.

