### Duration of Interventions and Justification for Creating a Usual Care Arm

In 2 intervention districts, the IHRPTM program will be implemented district-wide for 18 months, starting June-July 2024 and ending February-March 2026. The 18-month duration is necessary, as the introduction of different interventions in both the intervention districts requires 3‐6-month time. Also, for converting system level changes into outcomes is a time-consuming process [35]. Given the relatively short implementation period, we are not proposing a midline evaluation. However, the uptake, quality, and coverage of interventions will be continuously monitored through a robust monitoring system. Dipstick studies will be conducted depending upon the need. Any mid-course corrections will be based on findings from the baseline, monitoring data, and dipstick studies.

In the usual care arm, HWs will receive routine capacity-building sessions conducted by the state and the national governments. Pregnant women in both arms will have access to antepartum, intrapartum, and postpartum care programs provided by the state and the national governments. It implies that while general system strengthening interventions are provided in both the arms, the IHRPTM interventions are the only additional interventions confined to the intervention arm. At the community level, the IHRPTM program does not directly work with pregnant women in either arm. The control arm was included to isolate the effect of the IHRPTM interventions from the general system strengthening activities and to assess whether IHRPTM interventions had any incremental effect or value addition beyond what general system strengthening interventions alone can achieve. Thus, this study design ensures ethical equity while also allowing us to isolate the incremental effect of the IHRPTM program interventions by comparing changes in outcomes that go beyond improvements expected from broader system strengthening efforts.

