### Study Geography

For this study, the government of UP has identified Shravasti and Sambhal as the intervention districts to implement the program. Keeping in view the 2-arm nature of the study, the study team has identified 2 usual care arm districts that closely match with the intervention districts using latest socio-demographic, antenatal, and immediate postpartum care indicators for the district (NFHS-5, 2019‐2021) [13]. Identified Gonda as the matching usual care arm district for Shravasti. The distance between these 2 districts is less than 50 km. Identified Budaun as matching usual care arm district to Sambhal. The distance between these 2 districts is less than 100 km. Table 1 provides sociodemographic and ANC and delivery practices in 4 study districts, and Figure 2 depicts the 4 study districts. The matched control districts were approved by the government of UP.

**Table 1. T1:** Sociodemographic and health care–seeking profile of 4 study districts.

	Intervention arm districts		Usual care arm districts	
	Shravasti	Sambhal	Gonda	Budaun
Sociodemographic profile^a^				
Population (2011), n	1,117,361	2,199,774	3,433,919	3,681,896
Sex ratio of population, (females per 1000 males)	881	891	921	871
Urban population, %^b^	4	3	7	22
Tahsils, n	3	3	4	6
Villages, n	541	993	1817	2061
Literacy, %^b^	47	55	59	53
Scheduled caste population, %^b^	16.9	16.6	15.5	17.7
ANC^c^, delivery, and immediate postpartum care indicators (2019‐2021)^d^, %^e^				
Received at least 4 ANC visits	42.3	32.9	41.7	40.6
Mothers protected against tetanus toxoid	94.4	90.3	90.4	90.1
Mothers who consumed 100 iron-folic acid	16.6	21.3	17.2	15.9
Institutional births	80.4	74.2	81.8	72.3
Mothers who received postnatal care in 2 days	68.3	67.5	68.6	62.4
Mothers received MCP^f^ card	95.9	93.5	97.1	94.4

a Master data: Census 2011-state and district wise primary census abstract.

b These are census percentages.

c ANC: antenatal care.

d International Institute for Population Sciences (IIPS) and ICF. 2021. National Family Health Survey-5, India, 2019‐21: Uttar Pradesh. Mumbai: IIPS.

e Weighted percentages.

f MCP: Mother and Child Protection.

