### Survey Design

A multistage sampling approach will be used to select RDW from each arm. As census data at the village and ward level is old (2011), the accredited social health activist (ASHA) jurisdiction will be used to serve as a primary sampling unit (PSU). A total of 50 PSUs per district (100 per arm) will be selected using a 2-stage sampling approach. During baseline, the 2023 list of RDW in an ASHA’s jurisdiction served as the basis for the selection of a PSU. Assuming an average PSU will have 20 RDW, we expect to cover 1000 RDW per district (2000 per am) at baseline and end line surveys.

As part of the first stage of sampling, 50 PSUs in each district were allocated according to the proportion of the block population of the district. As part of the second stage of sampling approach, the allocated number of PSUs in a block was selected using the probability proportionate to size sampling technique.

During the baseline, in a selected PSU, the list of women who were delivered in the past 1 year, regardless of delivery outcome, and the delivery data maintained by ASHA and anganwadi workers (AWWs) served as the basis for identifying the eligible respondents for survey. This list by ASHA and AWWs was cross-verified with the list available with the ANM of the respective PSU, and a comprehensive list of RDW to be approached for interview was prepared. By adopting this strategy, we eliminated the need for doing households listing exercise to identify eligible RDW in the selected PSUs.

In a sampled PSU, all the households with eligible respondents (RDW) were approached by female investigator or supervisor for consent or assent for a face-to-face interview (Multimedia Appendix 7). All consented RDW participants were interviewed by female investigators, mostly in RDW’s home. To ensure 100% enumeration of eligible respondents in a PSU, a “snowballing” technique was also used with interviewed RDW to check if any peer RDW in her neighborhood was missed by the ASHA, AWW, or ANM list. If any new RDW is found through the snowballing technique, she was interviewed, provided she belongs to the selected PSU. Table 4 provides the inclusion and exclusion criteria used for selecting the respondents for the baseline and end line surveys in the 4 study districts of UP.

**Table 4. T4:** Inclusion exclusion criteria for respondents of baseline and end line surveys.

Respondent	Data collection method	Inclusion criteria	Exclusion criteria

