RDW^a^	Personal interview	Woman aged 15‐49 years, have had delivery during the past 1 year from the date of survey Details of such woman are available with ASHA^b^, AWW^c^, and ANM^d^ in the sampled PSU^e^ or woman was identified through snowballing technique from an interviewed RDW RDW who is resident of nonsampled PSU but had delivery in sampled PSU in past 1 year and is willing to participate in survey	All those who do not give consent to participate in the survey RDW listed by ASHA, AWW, and ANM, but not available for interview on days of survey Had delivery just within 3 days of survey Maternal deaths and RDWs with severe illness and unable to participate in interview
District officials and Specialist gynecologists	IDI	Currently serving in the stated position in the survey district	With less than 1 year of experience in the current position, in the survey district Who do not give consent to participate in the survey
Medical officer and ANM	SSI	Currently serving in the stated position in the sampled PHC^f^ and HSC^g^	With less than 1 year of experience in the current position in sampled PHC and HSC Who do not give consent to participate

a RDW: recently delivered women.

b ASHA: accredited social health activist.

c AWW: anganwadi worker.

d ANM: auxiliary nurse midwife.

e PSU: primary sampling unit.

f PHC: primary health center.

g HSC: health subcenter.

Using the above-stated survey design, tools, and inclusion and exclusion criteria, data for the baseline survey component of the impact evaluation of the IHRPTM program were collected during June-October 2024. Baseline qualitative data from system stakeholders were collected by ARMMAN researchers from 4 districts during June-August 2024. Baseline quantitative data were collected from >4000 RDW by around 75 female investigators and supervisors, during September-October 2024, from 200 PSUs, spread across 4 districts and 2 arms.

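### Table 4 admits non-resident women by place of delivery with no district limit, so a woman whose antenatal care was across an arm boundary can be counted under the wrong exposure; the size is unknown and may be nil

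*Protocol article*

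**What the plan says.** Under Survey Design, Table 4 lists the inclusion criteria for recently delivered women (RDW) at both baseline and end line. One of them admits an "RDW who is resident of nonsampled PSU but had delivery in sampled PSU in past 1 year", provided she is willing to take part. No district or arm condition is attached.

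The text of the same section treats women found by snowballing more strictly: "she was interviewed, provided she belongs to the selected PSU". The article does not define what belonging to a PSU means.

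Three other statements determine which arm is right for a given woman:

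- Exposure is assigned by district: "In 2 intervention districts, the IHRPTM program will be implemented district-wide for 18 months" (Duration of Interventions and Justification for Creating a Usual Care Arm).
- It reaches women only through health workers, since "the IHRPTM program does not directly work with pregnant women in either arm". The arms differ in one respect: "the IHRPTM interventions are the only additional interventions confined to the intervention arm" (same section).
- The outcomes arise from care in pregnancy. One example is the share of women with a high-risk condition who "received protocol-based management or referral from an ANM" (Hypothesis and Outcomes). Others are month of first diagnosis, the complete antenatal package, and resolution before delivery.

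On geography, Study Geography says of Shravasti and its control Gonda: "The distance between these 2 districts is less than 50 km". The other pair is under 100 km apart.

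**The concern.** Eligibility through the non-resident route depends on where the woman delivered. Her exposure depends on which auxiliary nurse midwife (ANM) and medical officer (MO) looked after her in pregnancy. Nothing in Table 4 stops a woman who had all her antenatal care in Gonda from entering the Shravasti sample because she delivered there, or the reverse. The article does not say to which arm such a woman would be assigned.

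At stake is the contrast that the control arm was set up to isolate. Each woman counted under the wrong exposure moves the DiD toward zero. The two enrolment rules also leave field teams unsure whether non-residents are in or out. If practice differed between rounds, the composition of the samples would change as well.

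**Working it through.** **The plan's own figure.** The only sample-size figure here is 1825 women per arm per survey, from n = z²p(1-p)/d². With z = 1.96, p = 0.05 and d = 0.01, n = 1824.7, so 1825. It reproduces and this point does not change it.

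**Who is misclassified.** Textbox 1 gives one accredited social health activist (ASHA) per 1000 population, and the PSU is one ASHA area. With the 2011 populations in Table 1 and 50 PSUs per district:

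- Shravasti: 1,117,361/1000 ≈ 1117 areas, of which 50 (4.5%) are sampled
- Sambhal: ≈ 2200 areas, 2.3% sampled
- Gonda: ≈ 3434 areas, 1.5% sampled
- Budaun: ≈ 3682 areas, 1.4% sampled

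So more than 95% of ASHA areas in every study district are nonsampled PSUs with the same exposure as the sampled ones. By origin of antenatal care:

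| Antenatal care was in | Enters intervention sample | Enters control sample |
|---|---|---|
| Same district, or other district of the same arm | correct | correct |
| District of the other arm | misclassified | misclassified |
| Non-study district of the state | misclassified (unexposed) | unexposed, so no dilution |

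The last row holds because the pilot runs in 2 of the state's 75 districts (Rationale for the Study).

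**Attenuation.** Let D be the true effect, and m_I and m_C the end line shares of each arm's sample whose actual exposure is that of the other condition. Assume a common effect and misclassified women who are otherwise like the rest. Apart from the shared trend, the intervention arm gains (1 - m_I)D and the control arm gains m_C·D, so

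observed DiD = D × (1 - m_I - m_C).

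Each m = s × c, where s is the share of the sample enrolled as non-residents and c the share of those whose antenatal care makes them misclassified. The documents give neither, so all values below are assumptions.

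| s | c | m = s × c | Factor, both arms affected (1 - 2m) | Factor, intervention arm only (1 - m) |
|---|---|---|---|---|
| any | 0 | 0 | 1.00 | 1.00 |
| 5% | 10% | 0.005 | 0.99 | 0.995 |
| 5% | 50% | 0.025 | 0.95 | 0.975 |
| 10% | 10% | 0.010 | 0.98 | 0.99 |
| 10% | 25% | 0.025 | 0.95 | 0.975 |
| 10% | 50% | 0.050 | 0.90 | 0.95 |
| 20% | 50% | 0.100 | 0.80 | 0.90 |

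For s of 5-10% and c of 10-50%, a true DiD of 10 points (an illustration, not a figure from the plan) would be seen as 9.9 to 9.0 points.

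**The case against.** The strongest reply is that living outside a sampled PSU is not living outside the arm. The programme covers whole districts and nearly all nonsampled PSUs share the sampled ones' exposure. This stands, and it limits the point to women who crossed an arm boundary for antenatal care.

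A reader might infer more than the documents support:

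- **That women are in fact in the wrong arm and the DiD is in fact attenuated.** No passage shows this. Distances under 50 km and under 100 km make crossing plausible but do not measure it.
- **That attenuation reaches 20%.** With both arms affected, this needs 10% of each arm's whole sample to be misclassified: for example, 20% non-residents with half of them crossing. That is a far stronger assumption than 10% non-residents.
- **That every woman delivering at a facility inside a sampled ASHA area becomes eligible.** Survey Design describes lists kept by ASHAs and anganwadi workers, cross-checked with the ANM's list, then household visits with interviews mostly at home. It describes no sampling from facility registers, so the 72-82% institutional birth rates in Table 1 do not indicate the size of this group.
- **That selection probabilities are undefined.** The route covers residents of nonsampled PSUs, so such a woman cannot also enter that sample through her home PSU. What remains is a weighting question of the kind an analysis plan commonly handles.

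It can also be said that the snowballing condition governs one enrolment route and the non-resident line another, so they need not conflict over the same woman. That is fair as far as it goes. But belonging is undefined, and Table 4 also lists snowballed women without the condition, so the wording still needs reconciling.

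Finally, baseline is complete, and Table 3 lists neither usual residence nor district of antenatal care. This does not remove the point, but it limits the remedy.

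**Conclusion.** The point holds in a limited form. Table 4 contains an enrolment route based on delivery place, without a district limit, for outcomes and an exposure that depend on antenatal care, and it sits badly with the snowballing condition in the text. The route can place women under the wrong exposure, and any such woman biases the DiD toward zero.

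The size is not known. The factor is 1.00 if all non-residents come from the same district, and about 0.99 to 0.90 under the assumed shares of 5-10% non-residents with 10-50% of them crossing in both arms. It is closer to 1 if only the intervention arm is affected. These figures rest on a common effect, on misclassified women resembling the others, and on assumed shares. The documents would equally allow a negligible effect. This is an inexpensive improvement to the plan, not a demonstrated bias.

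**What to change.** 1. Reconcile Table 4 with the Survey Design text: limit the non-resident route to women whose usual residence in pregnancy was in the same district, and define belonging to a PSU.
2. At end line, record usual residence in pregnancy and district of antenatal care.
3. Apply the same restriction to baseline where the enrolment record or the Mother and Child Protection card photograph allows. The article says the photograph holds details of each visit but not that it shows the district, so check this first.
4. If baseline can be flagged, run the primary DiD on the restricted set in both rounds, with all enrolled women as a sensitivity analysis.
5. If it cannot, keep end line eligibility unchanged so that the rounds stay comparable, and report the restricted end line analysis as the sensitivity analysis. Restricting one round only would create a new composition difference in the DiD.
6. Report the number of non-residents by arm and round, and at end line how many had antenatal care outside the district, so that m_I and m_C can be estimated rather than assumed.

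The cost is a clarified eligibility line, two end line items, a check of baseline records and one additional analysis. The downside is a small loss of interviews and possibly incomplete flagging at baseline.

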### Ethical Considerations

#### Overview

Qualitative data at baseline and end line surveys will be collected by ARMMAN researchers using computer-assisted personal interview (CAPI) tools, while quantitative data will be outsourced to a professional data collection agency, with prior experience in collecting maternal and child health–related data in UP. At baseline, a 2-day meeting of the qualitative researchers was held to discuss specific nuances of each question of the qualitative tool, how to ensure uniformity while asking questions, distribution of qualitative data collection workload, etc. For the baseline RDW tool, the investigators and supervisors of the shortlisted agency were trained for 5 days by ARMMAN program’s research team on the following topics: IHRPTM program and its objectives, ethical practices to be adhered to while collecting data from RDW, how to and when to approach potential gatekeepers, which RDW are eligible for consent or assent, how to obtain consent or assent, how to collect data using CAPI technique; importance of privacy during data collection, confidentiality of data, data quality, and potential risks and mitigation measures. Baseline RDW data were collected by female investigators or supervisors using the CAPI tool. All the tools were translated into Hindi and back translated into English, to ensure accuracy and retain the meaning of questions and most of the questions in the background, ANC, and delivery care sections were tried and tested in other large-scale surveys like NFHS.

All listed RDW in a PSU were approached by a female investigator or supervisor for participation in the survey using the RDW tool (Multimedia Appendix 6). Only those RDWs who expressed interest to participate in the survey were interviewed after obtaining informed consent. Respondents who were literate and comfortable in reading the informed consent form were given the option to read the form themselves or the investigator read it aloud to them. Once informed consent is received, the survey began. If the respondent felt the time was not appropriate to participate in the survey, a convenient time was sought, and the investigator returned at the time specified by the respondent to conduct the interview. Prior to approaching RDW, the gatekeepers of RDW (village leaders, teachers, religious heads, household heads, etc) were sensitized about the study and the safety of the RDW participating in the study by supervisors. For minors, informed consent was attained from the adult guardian, with assent from the minor. While interviewing RDW with severe morbidities, the procedure involved the presence of a guardian during the interview. The informed consent was obtained from the participant in the presence of the guardian. If she is unable to answer or give a consent, the Mother and Child Protection card was copied with the consent of the guardian. Including severe HRP cases in the survey would provide us with specific signs and symptoms associated with severity of the HRP condition, including gaps in diagnosis and management of these cases. Excluding severe HRPs from survey preview may result in collecting data only from the mild or moderately severe cases, and such data are not representative of the actual situation on the ground; hence, we have instructed investigators to collect data from severe HRPs by adhering to stated ethical norms.

A few women with severe HRPs may get distressed during the interview. To handle distress, investigators were trained using real field examples in trauma-informed and empathetic interviewing techniques. This included training on how to create a conducive environment (private, quiet, and comfortable place) for interview. During moments of distress, investigators responded empathetically by saying things like, “I can understand the pain,” offering water or tissues or keeping silent for a while. Keeping in view the distress level (tearfulness, prolonged silence, nervousness, or withdrawal), the investigator stopped the interview until the RDW’s distress had fully subsided. The interview was resumed only when she indicated she was ready to continue.

